#### Preliminary analyses

Baseline characteristics in SDT-WL versus BWL will be examined for comparability on demographic, weight history, psychosocial, and behavioral measures using multilevel regression models to account for interdependence within dyads (i.e., the tendency for couple members to be more similar to each other than to other participants) [63]. The distributional properties of any continuously scaled variables will be examined to determine if normalizing transformations should be applied. If group differences are noted on any baseline variables they will be statistically controlled by employing such variables as covariates in outcome analyses.

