**Methods:**

Project TEAMS (Talking about Eating, Activity, and Mutual Support) is a randomized controlled trial testing a couples-based intervention, grounded in SDT, designed to change the social context of weight loss by training spouses to provide needs support for each other’s eating and physical activity behavior. Sixty-four couples will be randomized to either 6 months of behavioral weight loss treatment informed by SDT (SDT-WL) or to 6 months of standard behavioral weight loss treatment (BWL). Couples will attend weekly sessions for 6 months and will be assessed at 0, 3, 6, and 12 months. By bolstering needs support, SDT-WL is predicted to increase autonomous self-regulation and perceived competence and produce greater weight loss and maintenance than standard behavioral treatment. Exploratory analyses will examine the SDT process model prediction that the influence of needs support on treatment outcomes will be mediated by autonomous self-regulation and perceived competence.

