##### Recruitment, screening, and randomization

Couples will be recruited through advertisements in the local media and screened by phone for preliminary eligibility. If eligible, couples will be invited to an in-person orientation where detailed information about the study will be provided and informed consent obtained. Once baseline assessments are completed, eligible couples will be randomized via a simple, variable-block length randomization, which ensures fairly equal allocations and will make it difficult to guess future assignments.

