### Statistical analysis

#### Sample size, power and effect size

We will have 80% power for a two-tailed test at alpha = .05 to detect an effect size equal to d = .71 at the dyad level, and .62 at the individual level (adjusting for interdependence within dyads) [63] for our primary weight loss comparison. Although our statistical power is limited, we will be able to calculate the 95% confidence interval around the point estimate of the SDT-WL intervention effect that will allow us to conduct an accurate power analysis for a future efficacy trial.

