#### Statistical analyses to support the primary aims

Structural regression models that treat couple members as nested within dyads will be used to examine primary aims of the study [63] using the R package lavaan [64]. To analyze the primary hypothesis that SDT-WL versus BWL will achieve greater increases in perceived needs support from baseline to 6 and 12 months, needs support at each time point will be used as an outcome variable, controlling for baseline needs support. Full information maximum likelihood estimation (FIML) will be used to account for missing data. Any relevant between- and within-dyad covariates based on the preliminary analyses described above will also be included in the analysis. Dyadic analysis will examine primary hypotheses that SDT-WL versus BWL will display greater autonomous self-regulation and competence for healthy behaviors (i.e., eating and physical activity) and greater weight loss at 6 and 12 months using the same strategy outlined above.

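### Covariates for the primary models are chosen by observed baseline differences between randomized arms, which leaves the model open and costs a modest amount of precision

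*Protocol article*

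**What the plan says.** Under *Preliminary analyses*, baseline characteristics in the two arms "will be examined for comparability on demographic, weight history, psychosocial, and behavioral measures using multilevel regression models". The consequence follows in the same paragraph: "If group differences are noted on any baseline variables they will be statistically controlled by employing such variables as covariates in outcome analyses". No size of difference, p-value or other threshold says when a difference counts as noted.

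Under *Statistical analyses to support the primary aims*, the result is carried into the main models: "Any relevant between- and within-dyad covariates based on the preliminary analyses described above will also be included in the analysis". What makes a covariate relevant is not defined.

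The one adjustment fixed in advance is the baseline value of the outcome: "needs support at each time point will be used as an outcome variable, controlling for baseline needs support". The weight hypothesis is handled in the same way ("greater weight loss at 6 and 12 months using the same strategy outlined above"), and the secondary aims reuse the procedure.

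Allocation is by couple: "eligible couples will be randomized via a simple, variable-block length randomization, which ensures fairly equal allocations".

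**The concern.** In a randomized comparison, a baseline difference between arms is a chance event. Looking for such differences and acting on them selects covariates for their correlation with arm. That is the wrong criterion, because a covariate improves precision by explaining the outcome. A variable that happens to differ between arms but explains nothing adds collinearity with arm and widens the interval. A variable that explains the outcome but happens to be balanced is left out, and its gain in precision is lost.

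The primary model also cannot be written down before the data are seen. With neither *noted* nor *relevant* defined, two analysts could apply the text to the same data and fit different primary models.

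This trial has little room for either cost. *Sample size, power and effect size* concedes that power is limited, and it gives the point estimate and its 95% confidence interval the job of sizing a future efficacy trial. That estimate should come from a model fixed in advance, with no avoidable variance.

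**Working it through.** **1. The plan's own figure.** Inputs: 64 couples (abstract), so 32 per arm at equal allocation; two-sided alpha .05; d = .71 at the dyad level (*Sample size, power and effect size*). The noncentrality is d × √(n/2) = 0.71 × √16 = 2.84 on 62 degrees of freedom. Power is 0.798, and the detectable effect at 80% is d = 0.711. The stated figure reproduces, with no slack.

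The within-couple correlation is not stated. The individual-level d = .62 implies it through d_ind = d_dyad × √((1 + ICC)/2), so ICC = 2 × (0.62/0.71)² − 1 ≈ 0.53. The checks below use .3 and .5 for the outcome.

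**2. How many variables are screened.** Table 2 lists about 29 baseline variables or instruments: 10 demographic and history, 10 anthropometric and behavioral (weight and height counted separately), 4 SDT, and 5 support and relationship. I take k = 25.

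**3. How often the rule changes the model.** Assume independent variables and a flag at p < .05. Neither assumption is in the protocol. P(at least one flag) = 1 − 0.95^k, and the expected number of flags is 0.05k.

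| k | P(at least one) | expected flags |
|---|---|---|
| 10 | 40% | 0.50 |
| 20 | 64% | 1.00 |
| 25 | 72% | 1.25 |
| 30 | 79% | 1.50 |

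**4. Cost of adjusting for flagged, non-prognostic variables.** The planned models nest spouses within dyads, so the check simulates 128 spouses in 64 dyads, with 25 independent noise covariates flagged at p < .05 and a generalized least squares fit.

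- Covariates measured on each spouse (covariate ICC 0 to .6): the variance of the arm effect rises by about 2–8%. By 64 × (1 − 1/ratio), this equals losing 64 × (1 − 1/1.02) ≈ 1.3 to 64 × (1 − 1/1.08) ≈ 4.7 couples.
- All 25 covariates essentially couple-level (ICC near 1): the rise is about 11–14%, or 6.3 to 7.9 couples.
- Covariates inter-correlated at .3: about 3%. With only 15 covariates (outcome ICC .5, covariate ICC .3): about 1%.

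Spouse-level covariates cost less because their slope is also estimated from differences within couples.

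**5. Precision forgone by omitting balanced prognostic variables.** This check uses one value per couple, with 25 covariates of which 3 are prognostic, and the baseline outcome in every model. The R² values are assumed.

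| R² of baseline outcome / of prognostic covariates | SD, plan's rule | SD, baseline outcome only | SD, fixed prognostic covariates |
|---|---|---|---|
| .05 / .15 | 0.253 | 0.243 | 0.230 |
| .30 / .20 | 0.217 | 0.211 | 0.184 |

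In the first row, power at d = .71 is 78%, 82% and 86%. In the second, power at d = .5 is 61%, 65% and 77%. These figures illustrate direction and order of size. They treat every covariate as couple-level, and the gain depends wholly on the assumed R².

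**6. Validity.** In the same simulations the rule gave no bias, and its type I error was 0.037 to 0.048.

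**The case against.** **This may be detail left to an analysis plan.** It is not. The article states a selection rule and applies it to the primary models. An analysis plan could define the threshold, but it would still be selecting by imbalance.

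**The text prescribes no significance test.** This stands as a matter of wording. The arms are examined and differences are noted, and the .05 used above is an assumption. It does not rescue the rule, because acting on an arm comparison is selection by imbalance at any threshold. In the one-value-per-couple check, a .20 threshold let in about 5 covariates and gave an SD of 0.221, against 0.182 for fixed prognostic covariates.

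**Not every flagged variable need enter every model.** This also stands. The word *relevant* is a filter, but an undefined one, so it adds discretion rather than removing it.

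**The primary models are largely fixed, and no validity harm is shown.** The baseline outcome is in every primary model. Selection uses baseline data and arm, not outcomes. A reader might infer that the rule biases the effect or inflates false positives. The article does not support that for mechanical use, and the simulations contradict it. The assurance does not cover judgement about relevance made once outcomes are visible.

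**The cost can be overstated.** A reader might take a variance rise of about 12%, or some 7 couples, as the single answer. That comes from one value per couple, whereas the planned models nest spouses within dyads. Likewise, a large loss from omitting one strong predictor needs a correlation with the outcome, beyond its baseline value, that no passage supports.

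**Sex would be a tempting example of a predictor left to chance.** It is a poor one. In mixed-sex couples (an assumption; eligibility does not restrict this) each dyad has one of each, so sex cannot be imbalanced between arms, and with complete data adjusting for it leaves the arm estimate unchanged. Baseline BMI largely duplicates the baseline weight already adjusted for.

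**Conclusion.** The point holds as one of efficiency and pre-specification. The rule selects covariates by chance association with arm and leaves the primary model open until the arms have been compared.

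The direct cost is modest: a variance rise of about 2–8% for spouse-level covariates and about 11–14% if all are couple-level. This assumes 25 independent non-prognostic variables and a p < .05 flag; it is lower with fewer or correlated variables. A further loss, of a size the article gives no means to fix, arises when predictive covariates are balanced and so omitted.

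The change should be made because it costs almost nothing and the trial's power is admittedly limited. It is not a threat to the validity of the comparison.

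**What to change.** - Delete the baseline-difference rule under *Preliminary analyses* and the sentence under *Statistical analyses to support the primary aims* that carries it forward.
- Keep the baseline value of the outcome in every model where one exists.
- Name in advance a short list of already collected covariates expected to predict the outcome beyond its baseline value, and include them regardless of balance. Age is one candidate; the eligibility section itself remarks that needs probably differ across the age range.
- Present baseline characteristics by arm descriptively.
- Label any adjustment prompted by an observed imbalance as a sensitivity analysis.

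The cost is analysis-plan wording and a few degrees of freedom. No new data or participants are needed.

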#### Statistical analyses to support the primary aims

Structural regression models that treat couple members as nested within dyads will be used to examine primary aims of the study [63] using the R package lavaan [64]. To analyze the primary hypothesis that SDT-WL versus BWL will achieve greater increases in perceived needs support from baseline to 6 and 12 months, needs support at each time point will be used as an outcome variable, controlling for baseline needs support. Full information maximum likelihood estimation (FIML) will be used to account for missing data. Any relevant between- and within-dyad covariates based on the preliminary analyses described above will also be included in the analysis. Dyadic analysis will examine primary hypotheses that SDT-WL versus BWL will display greater autonomous self-regulation and competence for healthy behaviors (i.e., eating and physical activity) and greater weight loss at 6 and 12 months using the same strategy outlined above.

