## Methods

### Study design (Fig. 1)

Couples will be randomized as a dyad to the enhanced needs support condition (SDT-WL) or to a more traditional model of spouse involvement (i.e., spouses attend groups but receive no training in providing autonomy support; BWL). All couples will receive 6 months of weekly weight loss group meetings and the same core information about diet and physical activity. In BWL, each member of the dyad will be encouraged to engage in healthy behaviors and weight loss efforts and to serve as a model or cue for desired behavior changes. In SDT-WL, the dyads will receive additional training in how to provide autonomy support for weight loss. Couples will be assessed at 0, 3, 6, and 12 months.

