#### Treatment components common to both conditions

##### Treatment length

In both conditions, the 6-month treatment program will be delivered in interactive weekly group sessions (check-in period, didactic information, and group discussion) lasting approximately one hour. This meeting schedule is consistent with best practices according to recent AHA/ACC/TOS guidelines [9].

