#### Treatment components specific to the SDT condition

The primary difference between conditions is that dyads in SDT-WL will receive additional training in how to provide needs support for each other’s weight loss efforts. Adapting effective strategies from the literature on needs supportive behaviors in educators, coaches, and healthcare providers [27–29, 32, 42–45], spouses will be encouraged to: 1) elicit and acknowledge the other’s perspectives, 2) minimize efforts to control, 3) use non-judgmental, non-critical language, 4) support each other’s initiatives for change, and 5) develop empathic responding as a substitute for evaluative praise or condemnation. This type of support is distinct from more directive forms of support, such as reminding a spouse of his/her goal or encouraging certain types of eating [21]. Couples will be taught basic concepts of needs support using an “ABC” model (Table 1) and will be provided opportunities to practice these new behaviors in group meetings and receive feedback from interventionists. Spouses will be encouraged to incorporate these behaviors into their relationship between sessions and to monitor targeted support behaviors in an ongoing fashion. A variety of clinical tools will be used to facilitate adoption of these behaviors including: 1) handouts of key points in the ABC model, 2) cartoon vignette dialogues similar to those used in Faber and Mazlish’s *How To Talk To Kids So Kids Will Listen and Listen So Kids Will Talk* [46] depicting unhelpful communication patterns and more effective ways of communicating, 3) role-plays (facilitated by the interventionists) to provide couples the opportunity to practice needs supportive behaviors and receive personalized feedback from interventionists, 4) group discussions of all the concepts, vignettes and other material relevant to autonomy supportive behavior, and 5) weekly written reflection on support provided and received from one’s spouse with examples shared at group sessions.

**Table 1 Tab1:** “ABCs” of Needs Support Training Objectives

Basic Concept	Training Goal	Example exercises
**A**sk to avoid assumptions	• Teach spouses to ask what would be most helpful • Teach spouses to discuss behaviors that promote weight loss and behaviors that sabotage weight loss.	• Have spouses discuss what would be most helpful; discuss what gets in the way of providing this support.

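### Both arms are treated in weekly groups, but the model and the power statement allow only for dependence within couples; if couples in the same group have correlated outcomes, standard errors are too small and d = .71 is optimistic

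*Protocol article*

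**What the plan says.** All references are to the protocol article.

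- **Unit randomised.** The couple (Study design), using "simple, variable-block length randomization, which ensures fairly equal allocations" (Recruitment, screening, and randomization).
- **Delivery.** In both conditions, "the 6-month treatment program will be delivered in interactive weekly group sessions" (Treatment length), made up of check-in, teaching and group discussion. In SDT-WL, couples also "will be provided opportunities to practice these new behaviors in group meetings and receive feedback from interventionists" (Treatment components specific to the SDT condition).
- **Groups sit inside arms.** The fidelity check asks raters to identify the condition of each sampled session (Quality control and safety procedures), so a session belongs to one condition.
- **Primary model.** "Structural regression models that treat couple members as nested within dyads will be used to examine primary aims of the study" (Statistical analyses to support the primary aims), fitted in lavaan with full information maximum likelihood (FIML). The secondary analyses reuse this procedure, and the baseline comparison also allows only for couples.
- **Power.** "We will have 80% power for a two-tailed test at alpha = .05" at d = .71 for dyads and .62 for individuals, the latter "adjusting for interdependence within dyads" (Sample size, power and effect size). That section admits limited power and gives the 95% confidence interval the task of informing the power analysis of a later efficacy trial.

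No section mentions dependence among couples who share a treatment group or an interventionist.

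**The concern.** Couples are allocated separately but treated together. Those in one group share a leader, peers and discussion over six months, which can make their weight and needs-support outcomes more alike than those of couples in other groups. Because groups are nested in arm, any between-group variance enters the difference between arms, while a model with only a couple level leaves it out of the standard error.

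Two things are at stake. One is the false-positive rate of every between-arm test. The other is the width of the confidence interval that the article treats as the trial's main product for planning. The article names the nesting structure and the only dependence adjustment behind its power figure. This is therefore an error structure that the article states, and not a detail left to a fuller plan.

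**Working it through.** **Inputs from the article.** 64 couples, near-equal allocation, so 32 per arm; two-sided alpha .05; 80% power; d = .71 (dyad) and .62 (individual).

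**Assumed inputs.** Couples per group m = 4 (8 groups per arm) or m = 8 (4 groups per arm). ICC = between-group share of the dyad-level variance, .01 to .10. The article gives none of these.

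**Step 1: reproduce the stated figures.** For independent couples, the noncentrality is .71/√(2/32) = 2.84. With 62 df, power is 79.8%, and the d giving exactly 80% is .711. The individual figure follows from d_ind = d_dyad × √((1 + ρ)/2). Setting .62 = .71 × √((1 + ρ)/2) gives ρ ≈ .525 within couples. Both figures are thus met with no allowance for groups.

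**Step 2: variance inflation.** The variance of the arm difference is multiplied by 1 + (m − 1) × ICC. For m = 8 and ICC .05 this is 1 + 7 × .05 = 1.35, so the true standard error is √1.35 = 1.16 times the independent-couples value. Across the assumed range the ratio runs from 1.02 (m = 4, ICC .01) to 1.30 (m = 8, ICC .10).

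**Step 3: type I error of the couple-only test.** Trials were simulated with no arm effect, using dyad means and a two-sample t-test that ignores groups. This stands in for the arm test of the planned model.

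**Step 4: detectable d at 80% power.** This was computed twice: with 62 df, which isolates variance inflation, and with (number of groups − 2) df, which is 14 for m = 4 and 6 for m = 8.

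| m | ICC | Inflation | Type I error, couple-only test | Detectable d, 62 df | Detectable d, group df |
|---|---|---|---|---|---|
| 4 | 0 | 1.00 | 5% | .71 | .75 |
| 4 | .01 | 1.03 | 5.3% | .72 | .77 |
| 4 | .02 | 1.06 | 5.7% | .73 | .78 |
| 4 | .05 | 1.15 | 6.7% | .76 | .81 |
| 4 | .10 | 1.30 | 8.6% | .81 | .86 |
| 8 | 0 | 1.00 | 5% | .71 | .84 |
| 8 | .01 | 1.07 | 5.8% | .74 | .87 |
| 8 | .02 | 1.14 | 6.6% | .76 | .90 |
| 8 | .05 | 1.35 | 9.1% | .83 | .98 |
| 8 | .10 | 1.70 | 13.5% | .93 | 1.10 |

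**Step 5: power at d = .71.** For m = 4, power falls from 79% to 69% over ICC .01 to .10 with 62 df, and from 74% to 64% with group df. For m = 8, it falls from 77% to 57% with 62 df, and from 63% to 45% with group df.

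**Step 6: separate the two causes.** For m = 8 and ICC .01, the rise from .71 to .87 is .16. Moving to 6 df with no clustering already gives .84, so about .13 of the .16 is the degrees-of-freedom penalty.

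**The case against.** The omission is plain; its consequence is conditional. A reader might infer that the planned intervals are certainly too narrow and that 80% power is certainly not delivered. The article does not support that: it gives no ICC, group size, number of groups or number of interventionists, and at a group ICC of zero the couple-only analysis is valid. With small groups and ICC .01 the harm is slight: 5.3% type I error and about one point of power with 62 df. Nothing says that group membership is fixed for six months, and changing membership would dilute the clustering. Role-play is described only for SDT-WL, so it cannot be cited as a source of correlation in both arms.

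A reader might also take the whole move from .71 to as much as 1.10 as the cost of clustering. Step 6 shows that it is not. The planned test itself would still reject in about 79% to 75% of trials at d = .71 (m = 8, ICC .01 to .10). It does so with an inflated false-positive rate, which is the real problem. Nor is the power arithmetic wrong: it is right for independent couples, and only that assumption is in question.

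Finally, the article is condensed, and nesting within dyads does not exclude a further level in a fuller plan. This is only a partial defence, because the power section also names couple dependence alone and its figure leaves no room for groups.

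**Conclusion.** The point holds in conditional form. The article fixes couple dependence as the only correlation in the outcome models and the power figure, although both arms are treated in groups nested within condition. If the group ICC is above zero, the couple-only standard error is too small, by about 1% to 23% over the assumed range. Type I error is then about 5.3% to 13.5%, and d = .71 at 80% power is optimistic: about .72 to .93 from variance inflation alone, or about .77 to 1.10 for a test with group-based df, whose starting value at ICC 0 is already .75 to .84. These sizes rest on 4 to 8 couples per group, ICC .01 to .10, equal groups and all 64 couples analysed. The direction needs only a positive ICC. The article's admission of limited power does not answer the point, because the confidence interval it relies on instead is affected too.

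**What to change.** 1. Record each couple's treatment group (and any change of group).
2. Account for group in every between-arm outcome analysis. Either add a random intercept for group with small-sample degrees of freedom (Kenward-Roger or Satterthwaite), or keep the lavaan/FIML dyadic model and use group-clustered standard errors with a small-sample correction.
3. In the power section, restate the detectable effect for the actual number of groups over a stated ICC range, showing variance inflation and the degrees-of-freedom penalty separately.
4. Report the estimated group ICC with its interval, which will be wide, so that the next trial can use it.

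The cost is a wider confidence interval, a less favourable detectable effect, a group variance estimated imprecisely because groups are few, and some change to the modelling set-up. A random-intercept model with adjusted df is a different framework from the planned lavaan models; clustered standard errors depart from it less. No extra couples, visits or treatment changes are needed.
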